## 3.2 Study Duration, Enrollment and Number of Subjects

This study will last for 4 total years. Year 1 will consist of organizing the study team and conducting focus groups. In Year 2, clinics will be randomized, and the educational intervention will be finalized for testing. The cluster-randomized intervention will begin in the 7th month of year 2 and last through the 6th month of year 3. Data analysis will be conducted in the remainder of year 3 and into year 4.

We expect the following number of participants:

- Focus Groups: 12 patients, 12 providers
- Web-based surveys: 120 providers
- Cluster-randomized trial:
  - Number of clinics (intervention & control): 20;
  - Number of patients (intervention and control): 3,000

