### **4.2 Screening/Baseline Visit Procedures and Observation Procedures for the Cluster-Randomized Trial:**

- (1) Randomize intervention and control clinics:** A list of clinics that are interested in participating will be compiled by the primary investigators. A member of the study team, [name], PhD, will use the random number generator built into SAS to randomize 10 clinics into treatment and 10 clinics into control groups. If the number of potentially eligible clinics exceeds 20, 20 clinics will be chosen at random, and this list will subsequently be divided into 10 random treatment clinics and 10 random controls. Results of randomization will be provided to the study coordinators, who will inform clinics of their status.

Data for all patients who meet inclusion criteria will be included in this analysis. This educational

intervention is intended to better inform providers in intervention clinics as to the fall-related risks associated with opioids and BZDs as well as best practices in deprescribing opioids and BZDs. A toolkit to support screening and deprescribing will also be provided to providers at intervention clinics. It is expected that providers will use this information to attempt deprescribing for any patients for whom they feel the benefits of deprescribing outweigh the risks. The study team will collect data from the EHR on all potentially eligible patients, regardless of any attempted deprescribing. The same data will be collected for patients who received care from treatment and control clinics.

**(2) Screen for risk of falling:** Intervention group clinics will be expected to screen all patients who appear on the baseline report for falls risk, questions if the patient has not already been screened previously, by using the STEADI screening questions. Each clinic will be allowed to determine how they will integrate these questions into the patient care process. Although the processes used to integrate the screening questions into patient care will vary across clinics, all clinics will be required to enter patient responses to the questions into the EHR, as is standard practice in all UNC HealthCare clinics.

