## 6 STATISTICAL CONSIDERATION

Statistical considerations are described below for the primary and secondary outcomes from the cluster-randomized trials. No statistical analysis will be conducted with focus groups, and the surveys will be analyzed using descriptive statistics and bivariate assessments for pre-post change in provider knowledge, skills, and attitudes in management of opioids and BZDs between intervention and control clinics.

All hypothesis tests that are observed and deemed to be not statistically significant will be reported as being inconclusive. All statistical estimates of population parameters will be tabulated along with corresponding confidence intervals (CIs) and/or standard errors (SE). All hypothesis tests and tests for power are two-sided with an overall alpha of 0.05, unless otherwise specified.

**6.1 Primary Outcomes: Opioid and BZD exposure,** as defined by changes in milligram equivalents over time across control and intervention groups as well as discontinuation of opioids or BZDs. Outcomes are described in more detail in Section 6.3.

**6.2 Secondary Outcomes: Risk of Falls,** as defined by differences in rate of falls over time across control and intervention groups and described in more detail in Section 6.3.

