### 6.3 Statistical Methods

**Primary Analyses:** We will examine between-group differences in opioid and BZD exposure associated with an increased risk of falls in the intervention and control groups. Analyses will be performed using the following intention-to-treat principle, and index dates for the intervention group will correspond to the date on which they first received any intervention-related clinical activity. Index dates for otherwise eligible patients from the control group will be chosen at random from each patients' set of clinic visits corresponding to an eligible intervention visit during the study period. Our primary hypotheses are:

- Relative to individuals in both control groups, individuals in both intervention groups will experience a significant reduction in the milligram equivalent exposure to opioids and BZDs during the 1-year follow-up period.

- Relative to individuals in both control groups, individuals in both intervention groups will experience a significantly greater discontinuation rate of opioids and BZDs during the follow-up period 181 to 360 days after index.

There are two overlapping groups of patients aged 65+ that will be included in this study: opioid users and BZD users. For each hypothesis, there will be separate models comparing the impact of the program on opioid users and BZD users. Patients who use both will appear in both models. To examine any differential impact of the program among patients who use both classes of medications, a sensitivity analysis will be performed and will include an indicator variable for patients who use both classes.

Generalized estimating equations (GEE, PROC GENMOD) will be used to create longitudinal pre-post model for the milligram equivalent exposure models. An identity link with a normal distribution will be used for milligram equivalent exposure. The functional form of the model is as follows:

$$\text{Eq. 1: } Y = \beta_0 + \beta_1 X_{\text{exp}} + \beta_2 X_{\text{period}} + \beta_3 X_{\text{exp} \times \text{period}} + \beta_n X_n + \epsilon$$

Where  $X_{\text{exp}}$  is the exposure group indicator,  $X_{\text{period}}$  is the pre-post indicator, and  $X_{\text{exp} \times \text{period}}$  is the period-by-treatment interaction indicator and, correspondingly,  $\beta_3$  is the parameter of the difference in outcome by period for the intervention group compared to the control.  $X_n$  represents a vector of covariates.

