## 6.4 Sample Size and Power:

### 6.4.1 Milligram equivalent exposure to opioids

Effect of various interventions on milligram equivalent exposure to opioids has shown mean reductions ranging from 31% to 49%. A GEE model (continuous outcome) with a total sample size of 3000 patients, each measured two times before and after intervention will have statistical power in the range of 0.865-0.999 to detect differences in means of 0.30 or higher in milligram equivalent exposure when the standard deviation is in the range of 1 to 3. Pre-period measurements will include the 12-month period prior to index, and post-period measurements will include the 12 months following index. This assumes that the baseline correlation between observations is 0.2 or higher and a 20% attrition rate will be observed. Another assumption is that we will assign subjects randomly to an intervention group and control group with an equal split between the two groups. Notably, if the standard deviation of observations is above 3.0 or if the attrition rate is greater than 20%, then our statistical power will drop significantly. All calculations were performed using PASS Software.

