### **6.4.3 Milligram equivalent exposure to BZDs**

Effect of various interventions on milligram diazepam equivalent per day exposure to BZDs has shown mean reductions ranging from 25% to 85%. If clinics are randomly assigned to a treatment group and a control group, with an equal number of patients in both groups, a GEE model with a total sample size of 3000 patients, each measured two times before and after intervention, will have statistical power in the range of 0.678-0.969 to detect differences in means of 0.25 or higher in milligram equivalent exposure when the standard deviation is below 2. Pre-period measurements will include the 12-month period prior to index, and post-period measurements will include the 12 months following index. This assumes that the baseline correlation between observations is 0.2 or higher and that we will observe a 20% attrition rate. Power increases for larger mean difference values and drops significantly at higher standard deviation values.

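### The dose power figures carry no allowance for randomising 20 clinics, and all four calculations in 6.4 use the trial-wide 3,000 although opioid and BZD users are modelled separately.

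*Protocol*

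**What the plan says.** **Unit of randomisation.** Section 4.2 (1) has a study team member "to randomize 10 clinics into treatment and 10 clinics into control groups". Section 6.4.1 says "Another assumption is that we will assign subjects randomly to an intervention group and control group". Sections 6.4.2, 6.4.3 and 6.4.4 each condition on clinics being randomly assigned, but give no ICC, cluster size, number of clusters or design effect. The only correlation in 6.4 is the one of 0.2 or higher between observations (6.4.1 and 6.4.3).

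**Sample size.** Section 3.2 gives the whole trial as "Number of patients (intervention and control): 3,000". Under section 3.3 a patient qualifies with at least one opioid or benzodiazepine. Section 6.3 states: "There are two overlapping groups of patients aged 65+ that will be included in this study: opioid users and BZD users". Each hypothesis gets a separate model per class, and only users of both appear in both models. Yet all four power statements start from 3,000; in 6.4.3, for example, "a GEE model with a total sample size of 3000 patients, each measured two times before and after intervention".

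**Stated power.**

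| Section | Outcome | Detectable effect | Power |
|---|---|---|---|
| 6.4.1 | Opioid dose | Difference 0.30 or more, SD 1 to 3 | 0.865–0.999 |
| 6.4.2 | Opioid discontinuation | Odds ratio 1.30–2.0 | 0.631–0.953 |
| 6.4.3 | BZD dose | Difference 0.25 or more, SD below 2 | 0.678–0.969 |
| 6.4.4 | BZD discontinuation | Probability difference 0.25–0.85 | 0.859–1.000 |

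The general rule in section 6 is: "All hypothesis tests and tests for power are two-sided with an overall alpha of 0.05, unless otherwise specified".

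**The concern.** Patients in one clinic share prescribers, and in this trial they also share the intervention. If their outcomes are correlated, 150 patients in a clinic carry less information than 150 independent patients, and the comparison rests on 20 units rather than 3,000. A power calculation without a clustering term describes a different design. Using the trial-wide total for each class-specific model is a separate inflation that would remain even if patients had been randomised individually.

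At stake is what a result on the primary outcomes means. Readers will use the stated power to judge whether the trial could have found an effect of the size it names. If that power belongs to a design that was not run, the judgement is misinformed.

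**Working it through.** **1. Inputs from the protocol.** Two-sided alpha 0.05; 3,000 patients; 20% attrition, so 2,400 patients or 1,200 per arm; 10 clinics per arm, so 3,000/20 = 150 per clinic, or 120 after attrition; correlation 0.2.

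**2. Reproducing the stated dose power with independent patients.** For a difference in pre-post change with k measures in each period and n patients per arm:

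SE = sqrt(4 × SD² × (1 − rho) / (n × k)); power ≈ Φ(d/SE − 1.96).

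| Section | d | SD | n per arm | k | SE | d/SE | Power | Stated |
|---|---|---|---|---|---|---|---|---|
| 6.4.3, low end | 0.25 | 2 | 1,200 | 1 | 0.1033 | 2.421 | 0.677 | 0.678 |
| 6.4.3, high end | 0.25 | 2 | 1,500 | 2 | 0.0653 | 3.827 | 0.969 | 0.969 |
| 6.4.1, low end | 0.30 | 3 | 1,500 | 2 | 0.0980 | 3.062 | 0.865 | 0.865 |
| 6.4.1, high end | 0.49 | 3 | 1,500 | 2 | 0.0980 | 5.001 | 0.999 | 0.999 |

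The matches need no clustering term and use the full 3,000 (or 2,400) in a single class model. The inputs are not unique. One measure per period with rho 0.6 and 1,500 per arm also gives 0.865 and 0.969. For 6.4.3, an SD of 1.35 with a design effect of 2.19 gives 0.678 as well.

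**3. Adding clustering.** DEFF = 1 + (120 − 1) × ICC. The standardised effect is divided by sqrt(DEFF), and power is taken from the noncentral t on 20 − 2 = 18 df. The ICC is **assumed**, since the protocol gives none; for dose it is the ICC of the change. The starting values are d/SE = 2.42 for 6.4.3 and, from the stated 0.865, 1.96 + 1.10 = 3.06 for 6.4.1.

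| ICC | DEFF | 2,400/DEFF | 6.4.3 (stated 0.678) | 6.4.1 (stated 0.865) |
|---|---|---|---|---|
| 0.001 | 1.12 | 2,145 | 0.58 | 0.78 |
| 0.005 | 1.60 | 1,505 | 0.44 | 0.63 |
| 0.01 | 2.19 | 1,096 | 0.34 | 0.50 |
| 0.02 | 3.38 | 710 | 0.24 | 0.35 |
| 0.05 | 6.95 | 345 | 0.14 | 0.20 |

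Part of the loss comes from the 18 df alone: with ICC 0 the two figures are 0.63 and 0.83. The 6.4.1 match in step 2 used 1,500 per arm, which is 150 per clinic. On that basis its column reads 0.77 / 0.59 / 0.45 / 0.31 / 0.17, so 120 per clinic is the milder choice.

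**4. Class share, without clustering.** If half the patients are BZD users (**assumed**), n = 600 per arm, SE = sqrt(4 × 4 × 0.8 / 600) = 0.1461, d/SE = 1.71 and power is 0.40 instead of 0.678. The two losses do not simply multiply, because a smaller class also means smaller clusters. With 60 BZD users per clinic and ICC 0.01, DEFF = 1.59, 1.71/sqrt(1.59) = 1.36, and power on 18 df is about 0.25.

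**5. Discontinuation.** The 6.4.2 and 6.4.4 figures could not be reproduced with the standard two-proportion calculations tried, nor 6.4.2 with difference-in-differences or time-averaged forms. It therefore cannot be shown whether they contain a clustering term, and no adjusted version of them is offered. For 6.4.4, a direct calculation for a difference of 0.25 keeps power at 0.98 or more at ICC up to 0.05, even with only 30% of the patients. That is above the stated lower bound of 0.859.

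**The case against.** **Three of the four sections name clinics.** This stands. A reader might infer that every power figure assumes individual randomisation; only 6.4.1 says so. For 6.4.2 to 6.4.4 the fault is the missing ICC or design effect. The numbers of clinics and patients are given elsewhere, so a mean cluster size can be derived, but an ICC cannot.

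**Reproduction is not proof.** This also stands. Other input sets give the same figures, and with 1,200 per arm, one measure per period and rho 0.2 the 6.4.1 low end would be 0.491, not 0.865. The match makes a design effect of 1 the natural reading of the dose figures. It does not establish it.

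**The size of the loss rests on assumptions.** It does. The ICC of a within-patient change may be smaller than a cross-sectional ICC, which is why the table starts at 0.001. A reader might infer that true power is well under half of what is stated. At ICC 0.01 the ratios are 0.34/0.678 = 0.50 and 0.50/0.865 = 0.58, so that reading fails at 0.01 and below.

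**Non-significant tests will be reported as inconclusive (section 6).** This limits the harm from misreading a null result. It does not make the stated power correct, or help someone judging whether the design can answer its question.

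**Conclusion.** The point holds in a bounded form. Three things are on the page and need no assumption: 6.4.1 contradicts 4.2 on the unit of randomisation; no part of 6.4 carries a clustering input; and 3,000 is used for each class model although it counts users of either class.

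The consequence is demonstrated for the two dose outcomes only, as a range: from 0.678 to between 0.58 and 0.14 for BZD dose, and from 0.865 to between 0.78 and 0.20 for opioid dose. This rests on an assumed ICC of the change of 0.001 to 0.05, equal clinics of 120 patients, and 18 df. The class-share loss, to about 0.40 for BZD dose, rests on an assumed share of one half.

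A reader might go further and conclude that the trial lacks power on all four primary analyses. The protocol does not support that. The 6.4.2 figures could not be checked, and at the large difference assumed in 6.4.4 power survives every ICC up to 0.05 that was tried.

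**What to change.** - Recompute 6.4.1 to 6.4.4 for 10 versus 10 clinics, with inference on about 18 df.
- Use separate expected counts of opioid users and BZD users per clinic, in place of 3,000 for each model.
- State an ICC range and its source. For dose it should be the ICC of the change, for example estimated from two consecutive historical 12-month EHR periods. A single pre-period yields only a cross-sectional ICC, which is a different quantity.
- Report the resulting power, or the minimum detectable difference, for each model, with enough inputs (measures per period, correlation, SD, attrition) for the figure to be reproduced.
- Correct the 6.4.1 sentence to say that clinics are randomised.

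The cost is protocol wording, an EHR count and a re-run of the power program. No extra patients are needed. The downside is that the stated power will be less favourable, at least for the dose outcomes.

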### 6.4.2 Discontinuation rate of opioids

According to a recent systematic review of literature, most opioid continuation rates are from relatively unreliable studies and can be anywhere between 54% to 100%. However, a recent study has found the odds ratio of opioid discontinuation in control versus treatment group to be 1.5 (95% CI [1.0-2.1]). If clinics are randomly assigned to a treatment group and a control group, with an equal number of patients in both groups, a GEE model (binary outcome) with a total sample size of 3000

patients, each measured two times before and after intervention, will have statistical power in the range of 0.631-0.953 to detect differences in odds ratios in the range of 1.30-2.0. There is significant drop in power for detecting differences in odds ratios below 1.3. Baseline probabilities in the treatment and control group are assumed to be in the range of 0.020-0.050 and we assumed a 20% attrition rate. For lower baseline probabilities of 0.010 in each group, the statistical power is in the range of 0.485-0.860 for detecting odds ratios of 1.3 or higher.

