**Cluster-Randomized Trial:**

- Primary: Longitudinal pre-post analysis to detect impact of program on dose of opioid and opioid discontinuation
- Secondary: Rate of falls

**Web-based surveys:** Descriptive statistics

---

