## 3.3 Study Population

**Inclusion Criteria:** To be eligible to participate in the study, clinics need to be affiliated with UNC HealthCare and have a patient population that includes patients 65 years of age or older. Targeted patients will be ambulatory (not institutionalized), aged at least 65 years old and taking at least one opioid or benzodiazepine medication listed in the design section for > 6 weeks, indicating they are at high risk for falls.

The UNC HealthCare outpatient clinics serve a diverse patient population, including women and minorities. The patient population served varies across clinics and geographical areas. UNC HealthCare coordinates care and manages care for more than 130,000 older adult patients in North Carolina. These beneficiaries are from all over the state. Females comprise 65.5% of the population. Approximately 52% are White, Non-Hispanic, 5.0% are Hispanic, 3.0% are Native American, 2.0% are Asian, and 38% are African American, Non-Hispanic.

To be eligible to participate in the patient focus group, participants need to be a patient in one of the intervention group clinics, 65 years of age and older, and taking at least one opioid or benzodiazepine chronically.

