### **5 SCREENING AND MONITORING EVALUATIONS AND MEASUREMENTS (how measurements will be made)**

In addition to the focus group instruments and web-based surveys, the development of which are detailed in Section 3, the following outcomes will be used for the cluster-randomized trial.

**The primary outcome for this study is opioid and BZD exposure, as measured by dose and discontinuation rate. A secondary outcome variable is the rate of falls.** We will also evaluate providers' satisfaction with the deprescribing toolkit. For clinicians providing services at an Intervention Group clinic, we will assess three outcome variables that reflect the process of service delivery: (1) whether or not their patients received education on opioids and BZD and their relationship to falls; (2) whether or not the deprescribing toolkit was utilized as part of the deprescribing process; and (3) whether or not HCPs referred to deprescribing toolkit recommendations concerning medication and non-medications to reduce the patient's risk of falls.

➤ **Opioid and BZD Exposure:** The primary outcome of this study will be exposure to opioid and/or BZD. This will be measured in two ways: (1) dose and (2) discontinuation. We will convert all opioid prescriptions to morphine milligram equivalents (MME), and all BZD prescriptions to diazepam milligram equivalents (DME). The method for calculating MME is well-established, and recommended by the CDC for evaluating opioid-related complications. Calculating DME is analogous, and has been used in previous work to evaluate exposure to BZD and has been used previously to evaluate success of discontinuation interventions. For each class of medications, we will calculate milligram equivalents for all observable prescriptions in the 12 months prior to the index and in the 12 months

post-index. To create a more conservative estimate of the impact of the intervention, we will assume that any authorized refills were filled. [DATA SOURCE: Epic EHR]

Discontinuation will be defined as a lack of opioid or BZD prescription from 181 to 360 days after the index. It is acknowledged that the intervention may not have an immediate impact on opioid and BZD discontinuation as prescribers taper patients' doses down, therefore a gap is given to allow for tapering in advance of discontinuation. [DATA SOURCE: Epic EHR]

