### **6.4.4 Discontinuation rate of BZDs**

A systematic review of literature has demonstrated discontinuation rates between 27-80% for interventions to reduce exposure to benzodiazepines. If clinics are randomly assigned to a treatment group and a control group, with an equal split between the two groups, a GEE model with a total sample size of 3000 patients, each measured two times before and after intervention, will have statistical power in the range of 0.859-1.000 to detect differences in post-intervention event probabilities in the range of 0.25-0.85. There is significant drop in power for detecting group differences below 0.25. Baseline probabilities in the treatment and control group are assumed to be in the range of 0.010-0.050 and we assumed a 20% attrition rate.

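### Discontinuation is defined only after index, but its power is computed from a before-and-after model with a 1–5% baseline that the endpoint does not have

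*Protocol*

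**What the plan says.** Section 5 makes discontinuation one of the two measures of the primary outcome: "Discontinuation will be defined as a lack of opioid or BZD prescription from 181 to 360 days after the index". The same section gives milligram equivalents a value for the 12 months before index and another for the 12 months after. Discontinuation gets no pre-index counterpart.

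Section 3.3 targets patients "taking at least one opioid or benzodiazepine medication listed in the design section for > 6 weeks", so every entrant is a user.

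Section 6.3 words the second primary hypothesis as a between-group difference, a "significantly greater discontinuation rate of opioids and BZDs during the follow-up period 181 to 360 days after index". The pre-post GEE of Eq. 1 "will be used to create longitudinal pre-post model for the milligram equivalent exposure models". The secondary analysis extends it, with a changed link and distribution, to falls.

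Three places describe discontinuation differently:

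- The synopsis lists as primary a "Longitudinal pre-post analysis to detect impact of program on dose of opioid and opioid discontinuation".
- Section 6.4.2 powers opioid discontinuation with "a GEE model (binary outcome) with a total sample size of 3000" patients, each measured before and after intervention. It states: "Baseline probabilities in the treatment and control group are assumed to be in the range of 0.020-0.050". Power is given as 0.631–0.953 for odds ratios of 1.30–2.0, and 0.485–0.860 at a baseline of 0.010.
- Section 6.4.4 uses the same before-and-after structure for BZDs: "Baseline probabilities in the treatment and control group are assumed to be in the range of 0.010-0.050". Power is given as 0.859–1.000.

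**The concern.** The power sections condition on the probability of being discontinued before the intervention. Under section 5 that event has no definition, and patients enter because they are taking the drug. Two of the four primary analyses (discontinuation of opioids and of BZDs) therefore have power statements about a different quantity from the one to be tested.

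Two things are at stake. First, the quantity that does drive power, the control-arm proportion discontinued on days 181–360, is never stated, so a reader cannot tell whether 3,000 patients are enough. Second, an analyst who follows the synopsis and the power sections literally would set up an arm-by-period model on the odds-ratio scale, and that model breaks down when there are no pre-index events.

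**Working it through.** **Inputs.** From the protocol: 3,000 patients, equal split, 20% attrition, two-sided alpha 0.05, odds ratios 1.30–2.0. Patients per arm: 3,000 × 0.8 / 2 = 1,200. This follows the protocol in counting all 3,000 in each drug class. Section 6.3 describes two overlapping user groups, so the number in one class may be smaller. Assumed, because the protocol gives no value: control discontinuation on days 181–360 of 2% to 46%. The upper end is 1 − 0.54, from the 54–100% continuation cited in section 6.4.2.

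**1. Can the baseline mean the control arm's post-index rate?** Section 6.4.4 lists post-intervention event probabilities of 0.25–0.85 separately from the baseline probabilities, and section 6.4.2 gives baselines for both groups. So the baseline is a pre-intervention value.

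**2. Attempt to reproduce the printed opioid power.** Wald test of the log odds ratio in the post window:

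- treated probability q = OR·p / (1 − p + OR·p)
- SE² = 1/[n p(1−p)] + 1/[n q(1−q)]
- power = Φ(ln OR/SE − 1.96), plus a negligible opposite tail

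Example: p = 0.05, OR 1.3, n = 1,200 gives q = 0.064, SE = 0.177, ln 1.3/SE = 0.262/0.177 = 1.48, power 0.32.

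| Model, 1,200 per arm | OR 1.3, p = 2% to 5% | OR 2.0, p = 2% to 5% |
|---|---|---|
| Post window only | 0.16 to 0.32 | 0.78 to 0.99 |
| Arm-by-period interaction, within-patient correlation 0.2 | 0.11 to 0.21 | 0.52 to 0.87 |
| Printed | 0.631 to 0.953 over the whole OR range | |

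At a baseline of 0.010 and OR 1.3, no variant tried (one- or two-sided, 1,200 to 3,000 per arm, several correlations, time-averaged or interaction) exceeded 0.285, against a printed minimum of 0.485. With correlation 0.8 two corners come close (0.618 and 0.970), but the full range of that model is 0.306–1.000. Section 6.4.2 gives no within-patient correlation, so failure to reproduce shows an incompletely specified calculation and does not prove an arithmetic error.

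For BZDs, 5% against 25% gives SE = √[(0.05×0.95 + 0.25×0.75)/1,200] = 0.014 and z = 0.20/0.014 ≈ 14, so power is 1.00. The printed lower end of 0.859 is not recovered either.

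**3. What happens to an odds-ratio interaction with no pre-index events?** The estimand is [logit p(T,post) − logit p(C,post)] − [logit p(T,pre) − logit p(C,pre)]. With both pre values at zero, the second bracket is −∞ minus −∞, which is undefined. A logistic model with arm, period and their interaction, fitted to simulated data with 1,200 per arm and no pre-index events, gave an intercept near −27.6 and an interaction SE of about 24,000. The post-only log odds ratio from the same data had an SE of 0.095 (control 20%) to 0.275 (control 2%).

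**4. Power for the endpoint as defined.** Same formula as step 2, clinic clustering ignored:

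| Assumed control proportion, days 181–360 | OR 1.3 | OR 1.5 |
|---|---|---|
| 2% | 0.16 | 0.33 |
| 5% | 0.32 | 0.65 |
| 20% | 0.76 | 0.99 |
| 46% | 0.89 | 0.999 |

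Clustering by clinic would lower every entry.

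**The case against.** The strongest reply is that the analysis is sound and only its description is loose. A reader might infer that a primary outcome cannot be analysed at all. The documents do not support that. Eq. 1 and its interaction are assigned to milligram equivalents and falls, no passage writes an interaction for discontinuation, and the section 6.3 hypothesis is already a post-window comparison that can be estimated. The absence of a written model for this outcome may be made good in the statistical analysis plan and is not held against the protocol.

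Three further limits stand:

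- Non-identifiability belongs to the logit or odds-ratio scale. On an identity link with zero pre-index events, the interaction is simply the post-period risk difference.
- A mirrored window of 181–360 days before index could contain patients without a prescription, because six weeks of use is enough to enter. That would measure recent starting and not stopping, and the protocol does not define it. So it does not supply the missing baseline.
- The synopsis line names opioid discontinuation only. For BZDs the pre-post framing rests on section 6.4.4 alone.

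None of this touches the power sections. They state a baseline probability and a before-and-after measurement in plain terms, and both conflict with sections 5 and 6.3.

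**Conclusion.** The point holds as a conflict within the protocol. Sections 3.3, 5 and 6.3 describe a post-index endpoint in existing users; the synopsis and sections 6.4.2 and 6.4.4 describe a repeated binary outcome with a 1–5% starting value. The printed powers for two of the four primary analyses therefore do not describe the endpoint as defined.

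Whether the trial is well or poorly powered for discontinuation cannot be settled from the document. At OR 1.3 the answer moves from about 0.16 to 0.89 over control proportions of 2% to 46%, and at OR 1.5 from 0.33 to 0.999. These figures assume 1,200 analysable users of the class per arm and independent patients. The conflict itself rests on the text and needs no assumption.

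**What to change.** In the synopsis, section 6.4.2 and section 6.4.4, describe discontinuation as a post-index comparison between arms of the proportion discontinued on days 181–360. Make it in all eligible users of that class, accounting for clinic and adjusting for pre-index dose. Delete the baseline probabilities of 0.01–0.05 and the before-and-after wording for this outcome. Restate power over a range of assumed control-arm proportions for days 181–360, with clinic clustering included.

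Do not narrow the comparison to patients with current supply at index. Section 6.3 sets index dates differently in the two arms after randomisation, so that restriction could unbalance them, and it would depart from the stated intention-to-treat principle.

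The cost is wording in three places and two power calculations, with no new data. The drawback is that the restated power may be less favourable than the printed figures.
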